**Rationale**

There is now a pandemic of diabetes affecting all areas and races, including the young and the old. Diabetes reduces life expectancy by 6 years especially in young people and increases vascular, renal, cancer and all-cause death by 1.3-3 folds. Compared to their white counterparts, non-Caucasians are at higher risk for developing diabetic kidney disease (DKD) which substantially increases risk of cardiovascular diseases (CVD) and all-cause death.

In clinical trial settings, control of blood pressure, blood glucose and blood lipids as well as inhibition of the renin angiotensin system (RAS) has been shown to reduce albuminuria, slow rate of decline in renal function and reduce risk of CVD and end stage renal disease (ESRD). In a post hoc analysis of the Treating to New Target Trial, treatment with 10 mg and 80 mg atorvastatin was associated with increased eGFR, more so in the high dose group. Yet, in most national and international surveys, less than 30% of patients were treated to target and/or received life-saving drugs such as statins and RAS inhibitors with an even lower percentage of patients treated to multiple targets. Apart from clinical inertia, 30-50% of patients treated with chronic medications for silent conditions such as diabetes and hypertension were non-compliant and unable to benefit from these life-saving drugs.

Since 1995, using a trio team consisting of a doctor, nurse and data manager, the CUHK-PWH Diabetes Care and Research Team has established a diabetes registry using predefined protocols to document risk factors, complications, drug use and clinical outcomes. This ongoing registry comprising 10,000 patients has provided enormous insights into the natural history of diabetes and impact of appropriate drug use on clinical outcomes. Using a team approach, augmented by care protocols with periodic reminders, we were able to substantially increase the rate of attaining multiple treatment targets and reduce the risk of major endpoints including CVD, ESRD and death in these high risk subjects. In support of these findings, in a recent systematic analysis, quality improvement initiatives with particular focus on empowering patients to improve self care were associated with significant improvement in risk factor control.

In 2007, we designed a web-based internet program (Joint Asia Diabetes Evaluation (JADE)

Program) incorporating templates for data collection, validated risk engines and decision support to enable doctors to establish his/her diabetes registry for quality assurance and ongoing evaluation. The collection and organization of these data into an easy-to-read format which displays individualized risk profile, trends of risk factor control with decision support has reduced clinical inertia and empowered patients with better self care. Upon reassessment at 1 year after enrolment, 30% of patients had meaningful reduction in risk factors (e.g. 0.5% for A1c, 30% for LDL-C, 10 mmHg for systolic BP, 3% for body weight) and improved rate of attainment of treatment targets.

### **Hypothesis**

- Patient empowerment and team-based care augmented by the JADE program with features of risk stratification and decision support improves multiple risk factor control in Asian type 2 diabetic patients with chronic kidney disease
- Attaining multiple treatment targets reduces all diabetes-related endpoints in these high risk patients

### **Objectives**

- To use the JADE program to set up a diabetic kidney disease (DKD) registry and document control of risk factors and care standards in real practice in Asian type 2 diabetic patients
- To use the JADE program with features of risk stratification, feedback, recommendations and decision support to empower doctors and patients to make informed decisions
- To use a team approach augmented by the JADE program to treat to multiple targets and reduce all diabetes related clinical outcomes

### **Inclusion criteria**

- Type 2 diabetic patients with serum creatinine above 30% upper limit of normal of the laboratory range and/or estimated glomerular filtration rate (eGFR) < 65ml/min/1.73m^2; or type 2 diabetic patients with both eGFR between 60 to 90ml/min/1.73m^2 and urine albumin creatinine ratio (ACR) ≥ 25 mg/mmol.
- Willingness to return for regular follow up visits

### **Exclusion criteria**

- Inability to give informed consent
- Life threatening condition with reduced life expectancy
- Patients on dialysis or eGFR < 15 ml/min/1.73

### **Study design**

This will be a multicentre randomized translational program to compare the effects of usual care (UC) versus empowered care (EC) versus team-based, empowered care (TEC) on risk factor control and clinical outcomes in 3000 patients with DKD in Asian countries.

## **Setting**

All patients will be recruited from high volume clinics in Asia led by diabetologists or nephrologists or cardiologists or internists. Each centre will consecutively recruit 300 patients with DKD and randomize them to UC (n=100), EC (n=100) or TEC (n=100) groups. After giving written informed consent, they will be randomized using sealed envelope, opened by an independent personnel, containing randomly generated computer codes for group assignment. All patients will undergo comprehensive assessments including examination of eye and feet as well as collection of blood and urine samples at baseline and 1 year later in accordance to international recommendations. Each patient will be followed up at least for 1 year and assuming half year of set up and patient recruitment, the project will last for 1.5 years. At the end of 1.5 years, the clinical outcomes of all enrolled patients will be ascertained by telephone contact within 1 month of the due date of repeat assessment of the last recruited patient.

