### **Outcome measures**

- Primary outcome
  - attainment of at least 3 treatment targets defined as
    - $\text{A1c} < 7\%$
    - $\text{BP} < 130/80 \text{ mmHg}$
    - $\text{LDL-C} < 1.8 \text{ mmol/L}$
    - $\text{Triglyceride} < 1.7 \text{ mmol/L}$
  - Use of RAS inhibitors between the 3 groups

- Secondary outcomes
  - Incidence of all-diabetes related endpoints (vascular, cancer, non-vascular non-cancer and all-cause death) between patients who attain at least 3 targets versus those who do not
- Other outcomes
  - amongst the UC, EC and TEC groups
    - Absolute and % changes in A1c, lipids, BP and body weight
    - Absolute and % changes in eGFR and albuminuria
    - Use of medications including statins, RAS inhibitors and insulin
  - between patients treated to multiple targets and those without
    - Incidence of ESRD and all-cause death
    - Incidence of all CV events including stroke, acute myocardial infarction, heart failure, acute coronary syndrome, all-cause death
    - Incidence of all-site cancer and all-cause death
    - Use of medications including statins, RAS inhibitors and insulin
- Cost-effectiveness and quality of life analysis

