### **Sample size estimation**

Most surveys in developing areas (Asia, East Europe and South America) show that only 20-30% of patients were treated with statins or RAS inhibitors or attained 1 of the 3 ABC goals (A1c<7%, BP<130/80 mmHg and LDL-C<2.6 mmol/l) and only 3-10% attained multiple treatment

goals. Based on our experiences using the JADE Program which has enrolled more than 30,000 patients since its launch in 2007, the organization, presentation and communication of data in an easy-to-read format has empowered patients to improve compliance with better physical and psychological health.

The power analysis and sample size estimation (Appendices 3 and 4) was conducted using PASS 11 (NCSS, LLC. Kaysville, Utah, USA. [www.ncss.com](http://www.ncss.com)). We estimated the rates of attainment of multiple treatment targets to be 10%, 20% and 30% in the UC, EC and TEC groups respectively. A sample size of 1000 patients in each of the 3 groups will have >95% power to test the primary hypothesis using a 2-sided likelihood ratio test and taking into consideration of multiple comparisons (type I error set at 1%). We further estimated that patients in the UC group will at least have an event rate of 5% per year, and EC group will have a 37% risk reduction (i.e., HR=0.63). A sample size of 2000 in total (1000 in the UC group and 1000 in the EC group) will have 80% power to confirm the effect size at an alpha of 0.05 assuming a yearly attrition rate of 20% in each group, half year for enrolment and 1 year for follow up and no switch in intervention between groups. For the comparison of the TEC with the UC group, we take multiple comparisons into consideration, i.e., type I error at 2.5%. A sample size of 2000 in total (1000 in the UC group and 1000 in the TEC group) will have 80% power to confirm the effect size of 50% risk reduction (HR=0.50) assuming an attrition rate of 20% in each group, half year for enrolment and 1 year for follow up and no switch in intervention between groups. Thus, a total of 3000 patients, 1000 in each group, is needed to achieve the effect sizes with 80% power and taking into consideration of multiple comparisons.

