### **Statistical analysis**

All analyses will be performed using the Statistical Program for Social Sciences (SPSS). All data will be expressed as mean±SD or median (interquartile range) as appropriate. Skewed data will be logarithmically transformed. Analysis of variance, student's t test and Fisher's exact-test will be used for comparisons amongst the UC, EC and TEC groups, as appropriate. The Kaplan Miere estimator will be used to demonstrate the cumulative incidence of first diabetes-related event while Cox model with adjustment for covariables at baseline and during follow-up will be used to check their contributions to the observed risk reductions. A p-value <0.05 (2-sided) will be considered significant. Number needed to treat (NNT) for prevention of an event by the EC and TEC group will be calculated separately using survival functions.

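### Allocation is balanced within centre and the target variables are measured at baseline, but the tests named for comparing arms use neither: a valid, slightly conservative comparison that gives up a little precision

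*Protocol*

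**What the plan says.** The Study design section plans a three-arm comparison "on risk factor control and clinical outcomes in 3000 patients with DKD in Asian countries". Under Setting, "Each centre will consecutively recruit 300 patients with DKD and randomize them to UC (n=100), EC (n=100) or TEC (n=100) groups". At 300 per centre, 3000 patients means about ten centres. Allocation works as follows: "they will be randomized using sealed envelope, opened by an independent personnel, containing randomly generated computer codes for group assignment". Stratification by centre is not named, but a fixed 100 per arm in every centre implies it. The same section schedules the same comprehensive assessment, with blood and urine samples, at baseline and at one year.

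The primary outcome is binary: "attainment of at least 3 treatment targets defined as" A1c, blood pressure, LDL-C and triglyceride limits, with use of RAS inhibitors listed alongside.

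The Statistical analysis section says: "Analysis of variance, student's t test and Fisher's exact-test will be used for comparisons amongst the UC, EC and TEC groups, as appropriate". Covariates appear in one place only, the analysis of clinical events: "Cox model with adjustment for covariables at baseline and during follow-up will be used to check their contributions to the observed risk reductions". For sizing, "We estimated the rates of attainment of multiple treatment targets to be 10%, 20% and 30% in the UC, EC and TEC groups respectively", tested with a two-sided likelihood ratio test at a 1% type I error. Appendix 3 shows this to be an ordinary two-sample comparison.

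**The concern.** The design controls for centre and the analysis does not use that control. There is reason to expect centres to differ. The clinics are led by different specialties in several countries, and usual care is whatever each institution practises, with EC added on top of it. When allocation is balanced by centre but the test ignores centre, between-centre variation stays in the error term and the standard error is overstated.

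Baseline target status raises a similar issue. The eligibility criteria do not exclude patients who already meet three targets, and such patients may count as attained at month 12 in any arm. Leaving baseline status out loses some precision and leaves chance imbalance uncorrected.

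What is at stake is the width of the intervals and the exact size of the test. The validity of the comparison is not in question.

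**Working it through.** **1. The plan's own figures.** Inputs from Sample size estimation and Appendix 3: rates of 10%, 20% and 30%, two-sided alpha 0.01. Power = Φ[(|p1 − p2| − 2.576·√(2p̄(1 − p̄)/n)) / √((p1(1 − p1) + p2(1 − p2))/n)].

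- 20% vs 30%: 0.8606 at 500 per arm and 0.9801 at 800, both as printed.
- 10% vs 20%: 0.9693 at 500 and 0.9989 at 800, both as printed.
- 10% vs 30%: 1.0000, as printed.
- At 1000 per arm, 20% vs 30%: (0.1 − 2.576 × 0.01936)/0.01924 = 2.606, power 0.9954. The other two contrasts give 0.9999 and 1.0000.

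The claim of more than 95% power holds.

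**2. Effect of centre.** The Protocol gives no between-centre variance, so I assume centre effects that are normal on the logit scale with SD 0, 0.3, 0.5 or 1.0. The share of outcome variance due to centre is then 0, 1.4, 3.8 or 13.4% at a 20% rate, and 0, 1.8, 4.8 or 15.7% at 30%.

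The true variance of the arm difference uses only the within-centre part, whereas the pooled test uses the total. At a common rate of 20%, the true type I error is 2[1 − Φ(2.576/√(1 − share))]. For SD 0.5 this is 2[1 − Φ(2.627)] = 0.0086.

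Results for 20% vs 30%, the weakest contrast. The 800 per arm column applies the 20% attrition that the Protocol states for the event endpoint only.

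| Centre SD (logit) | True alpha, pooled | 1000 per arm: pooled / by centre | 800 per arm: pooled / by centre |
|---|---|---|---|
| 0 | 0.0100 | 99.5 / 99.6% | 98.0 / 98.1% |
| 0.3 | 0.0095 | 99.6 / 99.6% | 98.1 / 98.3% |
| 0.5 | 0.0086 | 99.6 / 99.7% | 98.2 / 98.5% |
| 1.0 | 0.0056 | 99.8 / 99.9% | 98.7 / 99.3% |

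**3. Effect of baseline status.** Assume 10% meet the criterion at baseline and half of them still meet it at month 12. At overall rate p, the others attain at (p − 0.05)/0.9. Variance share = 0.09 × d² / [p(1 − p)], where d is 0.5 minus that rate.

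| p | Others | d | Share | Equivalent sample, 1/(1 − share) |
|---|---|---|---|---|
| 10% (UC) | 5.6% | 0.444 | 19.8% | 1.25 |
| 20% (EC) | 16.7% | 0.333 | 6.3% | 1.07 |
| 30% (TEC) | 27.8% | 0.222 | 2.1% | 1.02 |

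Removing the EC and TEC baseline parts (0.09 × 0.333² = 0.0100 and 0.09 × 0.222² = 0.0044) from the within-centre variances, and treating the centre and baseline parts as additive, takes power at 800 per arm from 98.0 to 98.5% with no centre effect. At SD 0.5 it goes from 98.2 to 98.9%, and at SD 1.0 from 98.7 to 99.5%. Each gain is below 1 point.

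**4. Simulation.** Ten centres with 100 per arm, 10% baseline attainment, log odds ratio for baseline status 1.5 to 3, centre SD 0.3 to 1.0. For 20% vs 30%, Fisher's test had power of 99.3 to 99.6%, against 99.5 to 99.9% for Cochran-Mantel-Haenszel stratified by centre and baseline status. Fisher's type I error was 0.006 to 0.009, with Monte Carlo standard error about √(0.01 × 0.99/3000) = 0.0018.

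**5. Chance imbalance.** With 10% attaining at baseline and 1000 per arm, the SD of the between-arm difference in baseline status is √(2 × 0.09/1000) = 1.3 points. Multiplied by d, that is 0.6 points of outcome at the UC rate, 0.4 at the EC rate and 0.3 at the TEC rate, against planned differences of at least 10 points.

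**The case against.** The strongest objection is that covariates for the primary model usually belong in a statistical analysis plan, which is not at hand. That would settle the matter if the Protocol were silent. It is not: it names the tests for comparing arms and reserves covariates for clinical events, so a later plan that adjusted the primary outcome would depart from the stated method.

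Four stronger readings are tempting, and the documents support none of them.

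- A reader might infer that the primary test is fixed as a pooled Fisher's exact test. The Statistical analysis section lists three tests to be used as appropriate across all outcomes and does not tie Fisher's test to the primary outcome; the sizing uses a likelihood ratio test. What stands is that every named option lacks a centre or baseline term.
- A reader might infer that nothing in the plan is adjusted. The Cox model already allows baseline covariables, which could include centre. A log-rank test appears only in the Appendix 4 sizing.
- A reader might infer bias, a raised false-positive rate or a power shortfall. With individual randomisation and equal allocation within centres, centre does not confound the comparison. The error is towards conservatism, and power stays at 98% or more.
- A reader might infer that adjustment is worth about 25% more patients, above all for TEC vs EC. That figure holds only at the 10% UC rate. On the same inputs the EC and TEC rates give about 7% and 2%. Higher persistence under EC or TEC would raise this, but no figure in the Protocol supports assuming it.

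**Conclusion.** The point holds as a modest loss of precision. The named tests discard a balancing factor built into the design and a baseline measurement taken on the patients. Over the assumed range of centre variation, the pooled test's true type I error is about 0.006 to 0.010 against 0.01, and adjustment for centre and baseline status adds less than 1 point of power at 800 to 1000 per arm. The primary comparison stays valid and the sample size needs no change.

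The between-centre SDs, the 10% baseline attainment and the 50% persistence are my assumptions. The equal allocation, the three target rates and the 1% alpha are the Protocol's.

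**What to change.** In the Statistical analysis section, name the primary analysis: a logistic model for month-12 attainment with randomised group, centre and baseline attainment (or number of targets met at baseline), reporting a standardised risk difference with its confidence interval for each pair of arms. Give a Cochran-Mantel-Haenszel test stratified by centre as the simple check. State how this relates to the likelihood ratio test in the Sample size estimation section, so that the two sections agree. Stratify the Cox comparison of arms by centre.

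The cost is wording only. Centre is known for every patient and the baseline values are already collected. No extra patients, visits or measurements are needed, and Appendix 3 can stand as a slightly cautious sizing.

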## **Intervention**

### ***Usual care (UC) group***

After undergoing comprehensive assessment, all patients will receive UC in accordance to the practice of the health institution and return at 12 months for repeat assessment

### ***Empowered care (EC) group***

After undergoing comprehensive assessment, all patients will be given a JADE summary report with personalized risk prediction, treatment targets and decision support with explanation from the doctor and nurse (Appendices 1 and 2). In addition to receiving UC in accordance to the practice of the health institution, the nurse will telephone the patient 3-monthly to remind them to adhere to treatment, provide support and empower them to discuss with their doctors about their treatment needs and any concerns. No reports will be given to patients as part of these follow up contacts in the EC group. All patients will return at 1 year for repeat assessment.

### ***Team-based, empowered care (TEC) group***

Patients randomized to the TEC group will be followed up by a doctor-nurse team at least 3 monthly to achieve multiple targets recommended as A1c<7%, BP<130/80 mmHg, LDL-C<1.8 mmol/l, triglyceride<1.7 mmol/l and persistence with RAS inhibitors, but tailored to patients' risk profile. Between follow-up visits, a nurse will telephone the patients. The patients will also be given a JADE follow up report 3-monthly and return at 12 month for repeat comprehensive assessment.

| Group | N   | Month 0 | Month 1.5 | Month 3  | Month 4.5 | Month 6  | Month 7.5 | Month 9  | Month 12 |
|-------|-----|---------|-----------|----------|-----------|----------|-----------|----------|----------|
| UC    | 100 | CA/N    |           |          |           |          |           |          | CA/N     |
| EC    | 100 | CA/N/D  |           | N-Tel FU |           | N-Tel FU |           | N-Tel FU | CA/N/D   |
| TEC   | 100 | CA/N/D  | N-Tel FU  | N/D/TMT  | N-Tel FU  | N/D/TMT  | N-Tel FU  | N/D/TMT  | CA/N/D   |

CA=comprehensive assessment, N=nurse, D=doctor TMT=treat to multiple targets

## **Comprehensive assessment and data collection**

All investigators and nurses will attend a 1-day training workshop on the ‘what, why and how’ of structured care and patient empowerment using a team approach, how to use the internet-based JADE portal and how to explain the results to patients with appropriate follow up actions. The JADE portal provides structured templates to guide care providers to collect demographic, clinical, biochemical, quality of life and drug usage data in accordance to standards for diabetes care recommended by the International Diabetes Federation (IDF). The portal also enables doctors to establish a registry at their own clinic as a quality improvement initiative.

### ***Questionnaires***

A set of self-administered questionnaires (Appendix 5) for assessing quality of life and psychological distress will be given to patients in all 3 groups to complete when they undergo comprehensive assessments at baseline and at 12 months.

#### **(i) Quality of Life (QOL)**

QOL will be assessed with the EQ-5D-3L, the World Health Organization Quality Of Life-BREF (WHOQOL-BREF), and a Time Trade-Off (TTO) question.

- The EQ-5D-3L assesses 5 dimensions of quality of life, namely, mobility, self-care, usual activities, pain/discomfort and anxiety/depression. Each dimension has 3 levels: no problems, some problems, extreme problems. The whole instrument consists of 2 pages, including a 5-item descriptive system, and an EQ visual analogue scale (EQ VAS) for a person to indicate their best imaginable health state.
- The WHOQOL-BREF is a shortened and validated version of the WHOQOL, which is a cross-culturally applicable QOL assessment. It comprises 26 items and measures the broad domains of physical health, psychological health, social relationships, and environment.
- The TTO question consists of a horizontal line which is marked and labelled 0,1,2,...10 years. The TTO question reads as follows: “Imagine that you are told that you have 10 years left to live. In connection with this you are told that you can choose to live these 10 years in your current health state or that you can choose to give up some life years to live for a shorter period in full health. Indicate with a cross on the line the number of years in full health that you think is equal value to 10 years in your current health state.”. The TTO value is obtained by dividing the response to the above question by 10. The TTO question has been used in multiple health-related investigations.

#### **(ii) Psychological Distress**

Psychological distress will be assessed with the Patient Health Questionnaire-9 (PHQ-9) and the Depression Anxiety Stress Scale (DASS-21).

- PHQ-9 is a 9-item scale that assesses depression severity and can be used for depression screening in primary care settings. Its introduction reads: “Over the last 2 weeks, how often have you been bothered by any of the following problems?”. A sample item is

“Little interest or pleasure in doing things.” Response options range from 0 (“Not at all”) to 3 (“Nearly every day”). Higher scale scores indicate more severe depression. This scale has been validated and shown satisfactory reliability in research with Asian samples.

- DASS-21 is a 21-item scale that assesses depression, anxiety, and stress. Participants are asked to read each of the 21 items and rate on a scale of 0 (“do not apply to me at all”) to 3 (“applied to me very much, or most of the time”). A sample item is “I couldn’t seem to experience any positive feeling at all”. Higher scale scores indicate greater emotional distress. This scale has been validated and shown satisfactory reliability in research with Asian samples.

